## Abstract

**Background:**

The Maternal and Child Health (MCH) handbook is an integrated home-based record (HBR) designed to record in a single document all the information regarding health services provided to a pregnant woman and her child. The MCH handbook has the potential to support continuity of care which is key to strengthening maternal, newborn and child health. However, there is a lack of an integrated system to manage the health of pregnant women and young children on an ongoing basis in Angola. Thus, the Angolan Ministry of Health is partnering with the Japan International Cooperation Agency to build the capacity of healthcare providers through trainings and implementation of the MCH handbook to improve service utilisation. In this study, we will estimate the impact of an intervention package including distribution of MCH handbook and its supplementary interventions to women, on the utilisation of services provided at healthcare facilities from pregnancy through the postnatal and early childhood period.

**Methods:**

This study is a cluster randomised controlled trial involving public healthcare facilities across all the municipalities located in Benguela Province, Angola. All women who go to participating healthcare facilities and with confirmed pregnancy around the beginning of the trial period will be included in the study. Women will be randomised according to the municipality where their primary maternity and/or childcare services are located. The intervention package will consist of MCH handbook distribution at all public healthcare facilities, MCH handbook utilisation training for healthcare providers and community mobilisation for women on the use of the MCH handbook. The intervention will be administered to all women in the intervention arm while those in the control arm will continue the traditional use of two stand-alone HBRs. The primary outcome measure for this study is to compare the proportion of women who achieve a complete continuum of care in both study arms.

**Discussion:**

The findings from the study are expected to form a basis for revising the current trial version of the Angola MCH handbook and provide a framework for policy guiding nationwide scale-up and distribution of the MCH handbook.

**Trial registration:**

ISRCTN Registry ISRCTN20510127. Registered on 4 June 2019

## Background

The Republic of Angola, after almost 30 years of civil war, has made substantial economic and political progress in recent years [1], and such changes in the political, social and economic development of Angola directly affect population health. While the development of the health sector has not been universal within the country, the government and its partners are making continuous effort at improving access to health services [2]. The National Health System is today a landmark of a social policy geared towards human development [3], but there is still a long way to go. Health indicators are yet to reach adequate standards, and women and children’s health continues to suffer. Maternal health is an important indicator in determining the status of health in a country and maternal mortality remains high in Angola. According to the World Health Organization (WHO) estimates, approximately 477 maternal death occurred per 100,000 live births in 2015 [4], primarily due to preventable causes. Also, Angola remains one of the African countries with the highest burden of under-5 (81 deaths per 1000 live births) and infant (54 deaths per 1000 live births) mortality rates, despite a consistent decreasing trend in recent years [5]. Some of the factors contributing to the poor maternal and child health indicators in Angola include weak health management systems [6] and the lack of an integrated system to manage the health of pregnant women and young children on an ongoing basis.

Towards rebuilding and strengthening the primary health care in Angola, its Ministry of Health (MoH) with support from the World Bank formally launched the Municipal Health Service Strengthening Project and the campaign for the acceleration of maternal and infant mortality reduction in 2010 [7]. This involves providing universal access to a package of high-impact interventions, including antenatal care (ANC) and counselling for women, provision of insecticide-treated bed nets for pregnant women and children under five to prevent malaria, immunisations against vaccine-preventable childhood diseases, de-worming and delivery of essential micronutrients [1]. Care for women and children starting from pregnancy through childbirth into the babies’ childhood has been promoted to improve maternal and child health through a continuum of care (CoC) [8, 9]. Continuum of care involves the concept of an integrated system of care that guides and tracks mothers and babies over time, through a comprehensive array of health services involving all levels of intensity of care. Continuum of care for mothers, newborn and children forms the basis of health care in many high-income countries which also have the best maternal health indicators [8]. In contrast, health care is neither continuous nor integrated in many low-income countries, including Angola.

The Government of Angola recently developed the National Plan for Health Development 2012–2025 and prioritised pregnant women, infants and young children as the target population. With support from the United Nations (UN), Angola is also working to strengthen the health information system in the collection, processing and analysis of data [6]. A mechanism for attaining this goal involves an emphasis on strengthening institutional and management capacity, and capacity building for health workers through long- or short-term trainings. Given the political will, the Japan International Cooperation Agency (JICA), through its health sector cooperation, is providing support to the Government of Angola to enhance healthcare service delivery. Moreover, JICA is also supporting the MoH through its Technical Cooperation Project (TCP) “Project for Improving Maternal and Child Health Services through the implementation of the Maternal and Child Health (MCH) handbook”.

The MCH handbook is an integrated home-based record (HBR) and is part of a scheme designed to record, in a single document, all the information and data regarding health services provided to and the health conditions of a mother and her child during the course of pregnancy, delivery and after birth, such as maternal care and the child’s growth pattern and vaccination schedule [10, 11]. In addition to other uses, the MCH handbook functions as a self-learning material, has the potential to reduce the need for multiple health records [12] and supports improvements in CoC [13, 14]. As a result, the MCH handbook has been attracting more attention from health ministries and professional organisations as an effective tool for promoting a life course approach to health care [11].

Despite the potentially important benefits of implementing the MCH handbook, there is a dearth of high-quality studies to show its superiority to existing alternatives [15, 16]. Therefore, this study will estimate the impact of an intervention package including distribution of MCH handbook and its supplementary interventions to women, compared with the traditional use of two stand-alone HBRs the on utilisation of services provided at healthcare facilities from pregnancy through the postnatal and early childhood period.

## Methods

### Study objectives and design

This study is a two-arm cluster randomised controlled trial (cRCT) to estimate the impact of a community-wide distribution of the MCH handbook and its supplementary interventions to women, compared with the traditional use of two stand-alone HBRs on CoC completion and various MCH outcomes. The unit of randomisation in this trial is the municipality (cluster). Specifically, this study will (1) evaluate the impact of MCH handbook on CoC completion, (2) assess uptake and utilisation of MCH handbook by both families and healthcare providers in Angola and (3) assess the impact of MCH handbook distribution and utilisation on maternal and child health.

### Study site

The study will be carried out in Benguela Province, Angola. Benguela is situated in the west of the country. Benguela has 10 administrative divisions called municipalities and a population of approximately 2.6 million [17]—being the third most populous province in Angola. Its population is mostly ethnic Ovimbundu and the most widely spoken language besides Portuguese is Umbundo. The most populous municipalities in the province are Lobito, Benguela, Cubal and Ganda (in descending order) [17]. Agriculture, fisheries and livestock farming are the main economic activities of this population. Benguela was purposively selected for this study because of health indicators that are close to the national average, thus representing an ideal setting to show intervention impact on MCH outcomes and demonstrate feasibility for nationwide scaling up of MCH handbook in Angola.

### Cluster selection

This impact evaluation study will be conducted in all 10 municipalities of Benguela Province. Each municipality comprises health communes that form the health administrative units for the province. The number and level of care provided by healthcare facilities vary between the municipalities. There are currently 209 public healthcare facilities [18] serving health needs and providing maternal newborn and child health (MNCH) services across Benguela Province comprising 82 secondary- or tertiary-level hospitals and 127 primary healthcare units (Table 1). The primary healthcare level provides services including MNCH care and refers cases to secondary and tertiary healthcare level as needed.

**Table 1 Tab1:** Number of healthcare facilities in Benguela Province

Arm	Municipality	Level of care		Total
		Primary	Secondary/tertiary	
Intervention	Lobito	24	3	99
	Cubal	20	2	
	Chongoroi	16	1	
	Bocoio	17	1	
	Balombo	15	0	
Control	Benguela	30	5	106
	Catumbela	16	1	
	Baia Farta	15	0	
	Ganda	24	3	
	Caibambo	11	1	
Total		188	17	205

There were 116,032 pregnant women in Benguela Province with 95,950 registered births in 2015. Of these, about 38% of women attended ANC services at a healthcare facility ≥ 4 times [18]. Furthermore, ANC attendance varied by municipality whereby ANC service utilisation was highest in Benguela (60%), Chongoroi (48%) and Lobito (47%) and lowest in Balombo (15%) and Baia Farta (4%) in 2015. In the same year, the rate of facility-based deliveries in Benguela Province was limited to 45%, while 93% of children in the province were fully immunised [18]. Various factors, such as distance to the healthcare facility, affect women’s utilisation of MNCH services across the province [19].

### Participant cohort

The intervention will be administered to pregnant women through frontline providers of MNCH services in public healthcare facilities in Benguela. The impact of the intervention will be estimated by collecting data about maternal and newborn participants who seek care from participating facilities. All women pregnant at the beginning of the trial period and attending a public healthcare facility for MNCH services will be eligible for inclusion in the study. In order to ensure similar baseline characteristics among participant cohort across all municipalities, the study cohort will include all women confirmed to have become pregnant at the start of the trial implementation period. The participant cohort will be recruited at their first visit for any MNCH service consultation over the course of the study **(**Fig. 1). Based on the findings from a previous study [20], most pregnant women are expected to make their first visit to the healthcare facilities during the second trimester of pregnancy.

**Fig. 1 Fig1:**
[figure not shown]
Participant recruitment process and data collection team tasks

Prior to recruitment, study eligibility will be assessed and pregnant women who satisfy these criteria will be briefed about the trial and invited to participate. Consenting participants will then be registered and enrolled in the study. Figure 2 shows the study timeline according to the Standard Protocol Items: Recommendations for Interventional Trials (SPIRIT) diagram. For each registered participant, contact details will be collected in as many details as possible to enable follow-up home visits by the trial team. Written informed consent will be obtained from every participant joining the study prior to enrolment. Further, all participants will be assured of their rights to voluntary participation, privacy, confidentiality and free choice to withdraw from the study during the conduct of the trial in the process of obtaining informed consent (Fig. 3 in Appendix 1, Fig. 4 in Appendix 2).

**Fig. 2 Fig2:**
[figure not shown]
schedule showing enrolment, allocation, intervention, baseline and end-line assessments. MCH, maternal and child health; LMP, last menstrual period; PDD, probable delivery date; ANC, antenatal care; HBR, home-based record

### Eligibility criteria

Participants will be eligible to join the study if they are confirmed by a healthcare provider to have become pregnant at the beginning of the trial period, had her last menstrual period (LMP) on any date from 1 March to 30 April 2019 or probable delivery date (PDD) on any date between 1 December 2019 and 31 January 2020. Participants will be selected among pregnant women and mothers within the defined cohort on their first visit to public healthcare facilities for MNCH services. Pregnant women will be excluded if they decline to participate in the study or are planning to move out of the study area while the impact evaluation study is ongoing.

### Power analysis

This cRCT has three unit levels: the municipality, healthcare facility and the individual. A simulation-based power analysis was done in SAS software 9.4 (SAS Inc., Cary, NC, USA) using the generalised linear mixed model and taking these levels into consideration (Table 6 in Appendix 3). The power analysis was used to estimate the sample size needed to detect a 10% (25% in the intervention arm and 15% in the control arm) increase in the rate of CoC completion significant at 5% and assuming a 20% dropout rate. The intracluster correlation coefficients (ICC) used in this simulation-based power analysis were 0.010, 0.015 and 0.020 [21]; and assuming that the number of participants was 5000, 7500 and 10,000, the power ranged from 0.560 to 0.828. We also confirmed in the simulation that type 1 error does not inflate. On the basis of these calculations, we aim to recruit at least 10,000 participants. The target sample size in each municipality will vary depending on the population size.

### Randomisation and allocation concealment

This study is a two-arm study comprising an intervention arm and a control arm. The unit of randomisation in this trial is the municipality (cluster). Cluster randomisation was chosen due to the nature of the intervention and to minimise logistical and scientific difficulties associated with individual randomisation in large-scale longitudinal studies—such as contamination. Benguela Province consists of 10 municipalities of varying sizes—Baia Farta, Balombo, Benguela, Bocoio, Caimbambo, Catumbela, Chongoroi, Cubal, Ganda and Lobito. All 10 municipalities will be included in the study. Population size and basic characteristics of each of the 10 municipalities were taken into consideration during the randomisation process to ensure a balance of socio-demographic characteristics between both arms.

Municipalities were allocated to either intervention or control arms using block randomisation [22, 23] by an experienced statistician in two steps. To ensure a balance between the two study arms, we ordered the municipalities by population size then applied block randomisation as described by Gattellari et al. [24]. First, municipalities were sorted by size based on the 2014 population data provided by the National Institute of Statistics [25]. Using the data, five blocks comprising of two municipalities each were created in the order of population size. Second, municipalities were randomly allocated either to the intervention or to the control arm within each block using computer-generated results. In this step, a pair of 4-digit code assigned to each block was fed into a SAS program that automatically returned a response, assigning one of the municipalities in the block to the intervention or control arm. The statistician was unable to predict assignment to either study arm. Municipalities allocated to the intervention or control arms were revealed simultaneously to the study team and municipal authorities at the kick-off meeting marking the start of the trial.

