### Blinding (masking)

Blinding will not be feasible due to the nature of the intervention; thus, neither participants nor trial personnel will be blinded in this study. However, the data analyst will be blinded to the allocation.

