### Statistical analysis

The intervention arm (MCH handbook) will be compared to the control (traditional use of two stand-alone HBRs) in the main analysis. We will conduct descriptive analysis, and baseline data from the intervention and control arms will be analysed for comparability of baseline characteristics. Rates of missing data for each variable will be determined to assess the differences between the arms, and overall losses to follow-up will be determined. We will report reasons for losses within each arm and compare the reasons qualitatively.

We plan to measure intervention impact using two analysis sets: the intention-to-treat (ITT) set and the per-protocol analysis set (PPS). The ITT population will include all participants within the randomised municipalities analysed according to the municipality where they were first registered to receive MNCH services (i.e. discounting where they received second, third or fourth MNCH services) [33, 34]. The ITT population will be the primary analysis set, and all analyses will be conducted using this population unless otherwise stated. In the PPS, participant data will be analysed according to the treatment they actually received. Data from the participant with more than one MCNH service utilisation in the control arm will be included in the control arm regardless of the municipality of first registration for MNCH services in the PPS analysis.

The primary endpoint in this impact evaluation study is to compare the proportion of CoC completion achieved among mothers who received the MCH handbook in the intervention arm and those who received the traditional stand-alone HBRs in the control arm. We will evaluate the effect of the provision of MCH handbooks on CoC completion at the municipality level using a generalised linear mixed model (GLMM) assuming logit link and binomial distribution. All analyses will be based on complete case analysis. Regarding the number of healthcare service utilisations, the analysis will be conducted using survival analysis. We will also evaluate the intervention effects in a subgroup of participants based on socio-economic status, urban/rural residence and other baseline characteristics while accounting for cluster effect.

All analyses will be done using STATA (version 13 or higher, Stata Press, College Station, TX).

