### Data management and storage

All data collection processes will be standardised across the 10 municipalities. At each healthcare facility, pregnant women seeking MNCH services and eligible to join the study will be listed in the study register maintained by a data collector. Following enrolment, each woman will be given a unique identification number. A standardised tablet-based data collection form will be administered to each woman by trained study data collectors at baseline and follow-up. To ensure completeness of each record, virtually, all questions in the form are required, while at the same time ensuring participants right to voluntary participation. Completed forms will be uploaded to a secure server at the end of each day. The datasets will be password-protected and only accessible to the data manager.

We will not establish a third-party data monitoring committee due to the nature of the intervention and study design. However, periodic meetings involving all members of the study team will be held weekly to review the processes and progress related to the following: (1) participant recruitment and interviews; (2) completeness, accuracy and timeliness of uploading completed survey forms to secure server; and (3) any other logistical issues related to the study.

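### Women are recruited by unblinded staff after allocation is public, and the stated primary model has no baseline adjustment, so measured arm differences in who is recruited can carry into the primary effect

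*Protocol article*

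**What the plan says.** All places are in the Methods of the protocol article.

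- **Allocation.** Under Randomisation and allocation concealment, ten municipalities are paired by population size and one of each pair goes to each arm. "Municipalities allocated to the intervention or control arms were revealed simultaneously to the study team and municipal authorities at the kick-off meeting", which marked the start of the trial.
- **Recruitment.** Under Participant cohort, "The participant cohort will be recruited at their first visit for any MNCH service consultation over the course of the study". Eligibility criteria has a healthcare provider confirm the timing of the pregnancy, and excludes women who decline. Trial status gives recruitment from June 2019 to June 2020.
- **Blinding.** Under Blinding (masking), "neither participants nor trial personnel will be blinded in this study"; only the data analyst is blinded.
- **Intervention.** Under Intervention and in Table 2, community sensitisation and mobilisation of pregnant women on using the handbook is in the intervention arm only.
- **Denominator.** Under Outcome measures, completion of the continuum of care (CoC) is assessed among women recruited while attending antenatal care.
- **Purpose of the window.** Under Participant cohort, the cohort is restricted to women who conceived around the start of the trial "In order to ensure similar baseline characteristics among participant cohort across all municipalities".
- **Analysis.** Under Statistical analysis, "baseline data from the intervention and control arms will be analysed for comparability of baseline characteristics", and baseline characteristics also define subgroups. The primary model is a binomial mixed model with logit link on complete cases. No covariate is named.
- **Register.** Under Data management and storage, "pregnant women seeking MNCH services and eligible to join the study will be listed in the study register maintained by a data collector".

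**The concern.** Randomising municipalities makes the populations of the two arms comparable in expectation. It does not do the same for the women analysed when they are identified, approached and consented after the arm is known. Here the denominator of the primary outcome is formed after allocation, and one component of the package is directed at pregnant women in the community. Who attends, when they attend and who agrees can therefore differ by arm.

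A common conception window aligns calendar time and expected delivery date. It has no hold on attendance or consent, so it cannot ensure similar baseline characteristics.

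Comparing baseline characteristics shows a measured imbalance but does not correct it. If the primary model is fitted as stated, its estimate mixes the effect of the package on women's behaviour with any change in who was recruited. Care-seeking varied widely before the trial: the Cluster selection section gives about 38% of women with four or more antenatal visits in 2015, and names municipalities with antenatal attendance from 4% to 60%. There is thus a large pool of low users whose recruitment could differ between arms.

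**Working it through.** **1. Inputs from the article.** Completion "25% in the intervention arm and 15% in the control arm", a 10-point target; "significant at 5% and assuming a 20% dropout rate"; at least 10,000 women; ICC 0.010, 0.015 or 0.020; five municipalities per arm. Appendix 3 gives power at 10,000 women of 0.828, 0.674 and 0.605 for the three ICCs.

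**2. The plan's own figure.** No single simple calculation reproduces the whole power table. Equal clusters, no dropout and a paired t reference with 4 degrees of freedom give 0.808, 0.660 and 0.549; the first two are within about 2 points of the table and the third is not. Cluster sizes and facility-level variance are not given, so the table is neither confirmed nor refuted. The point does not rest on it.

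**3. Illustration A: extra low-propensity recruits in the intervention arm.** Let a share s of intervention recruits be extra women who complete CoC at r times the usual 25%. Both s and r are assumptions.

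Bias = s × 0.25 × r + (1 − s) × 0.25 − 0.25 = −0.25 × s × (1 − r)

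| s | r | Bias (points) |
|---|---|---|
| 0.05 | 0.5 | −0.63 |
| 0.10 | 0.5 | −1.25 |
| 0.20 | 0.5 | −2.5 |
| 0.20 | 0.3 | −3.5 |

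The observed difference would be 8.75 points in the second row and 6.5 in the last. Scaling the stated power of 0.828 by a normal approximation: its z-value is 0.946, and 0.946 + 1.96 = 2.906. Then 2.906 × 0.875 − 1.96 = 0.58, power about 0.72; and 2.906 × 0.65 − 1.96 = −0.07, power about 0.47.

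**4. Illustration B: more care-seeking women in the intervention arm.** Suppose care-seeking women complete CoC 20 points more often than others (assumed). A difference between arms of 5, 10, 15 or 20 points in their share gives a false risk difference of 0.20 × that share: 1, 2, 3 or 4 points.

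With no true effect, 4,000 women analysed per arm (10,000 less 20%, halved) and 800 per municipality, the design effect at ICC 0.010 is 1 + 799 × 0.010 = 8.99. For a 2-point bias (17% v 15%):

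SE = √[(0.17 × 0.83 + 0.15 × 0.85) / 4000 × 8.99] = 0.0246, and 0.02 / 0.0246 = 0.81

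The nominal 5% error rate then becomes:

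| False difference | ICC 0.010: normal / t, 8 df | ICC 0.020: normal / t, 8 df |
|---|---|---|
| 1 point | 7.0% / 6.5% | 6.0% / 5.8% |
| 2 points | 12.9% / 11.1% | 9.1% / 8.2% |
| 3 points | 22.6% / 18.7% | 14.2% / 12.1% |

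**5. Direction.** A and B point in opposite directions. In A, the same sign arises if reluctant women decline more often in the control arm; it reverses if they decline more often in the intervention arm.

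**6. Which baseline items can serve.** Under Intervention, the handbook is given at the first visit, which is also the recruitment visit. Table 3 places most of the baseline interview at the woman's home. Health behaviour and antenatal use recorded there may already reflect the intervention. Age, education, pregnancy history, household wealth and residence cannot.

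**The case against.** The strongest reply is that the article never calls the model unadjusted. It gives family, link and distribution, and covariate lists are often left to an analysis plan, which is not shown. That stands to this extent: a reader might infer that the trial has decided against adjustment, and the text does not support that. But the Statistical analysis section does assign roles to the baseline data, comparison of arms and definition of subgroups, and adjustment is not among them. Followed as written, it gives an unadjusted estimate.

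A reader might also infer that mobilisation is meant to bring women to facilities. The article describes it as being about use of the handbook. A change in attendance is plausible, not stated.

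There are safeguards. All women in the cohort are to be included, the date window limits discretion over eligibility, providers in both arms are trained to establish dates, municipalities are paired by size, and the required number of antenatal visits is scaled to gestation at first visit. These reduce staff choice and soften the effect of late presentation. None governs differential attendance or consent.

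Finally, adjustment is a partial remedy, since the mechanism is care-seeking propensity and the usual covariates are proxies for it. In a logit model it also changes what the odds ratio means. Both statements are correct, and the fix allows for them.

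**Conclusion.** The concern holds as a risk of recruitment bias that the stated primary analysis does nothing to reduce. Each step needed for it is in the article: public allocation, then unblinded recruitment and consent, one-sided mobilisation, and a denominator formed at antenatal attendance. The statement that the conception window secures similar baseline characteristics claims more than a window can deliver.

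The size is not known. The illustrative shifts, -0.6 to -3.5 points one way and 1 to 4 points the other, rest wholly on assumed shares and completion rates, and nothing in the article shows a difference between arms in attendance or consent. It would be wrong to conclude that the result will be biased, that bias would favour the handbook, or that adjustment would remove it. Open disclosure of allocation at kick-off is also not itself an error in an unblinded community intervention. It matters because recruitment follows it. This is a change that should be made, not one on which the trial's validity turns.

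**What to change.** 1. **Statistical analysis.** Make the primary mixed model adjusted for a short list fixed in advance: age, education, parity or pregnancy history, household wealth, and urban or rural residence. The baseline survey covers socio-demographic, household and pregnancy-history items, and the subgroup plan already uses socio-economic status and residence; that age and education are among the socio-demographic items is assumed. Leave out health behaviour, antenatal use and timing of first visit. Keep the unadjusted model as a sensitivity analysis.
2. **Effect measure.** Report an adjusted risk difference beside the odds ratio, because adjusted and unadjusted odds ratios do not estimate the same quantity.
3. **Recruitment by arm.** From the study register, report numbers listed and consenting, and gestation at enrolment.
4. **Participant cohort.** Reword so that the window is said to align the timing of pregnancies, not to ensure similar baseline characteristics.

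The cost is analysis-plan wording and one table, with no new data, staff or visits. Under the complete-case rule, women with missing covariates would be lost, so a simple handling rule is needed; almost all form items are mandatory, so few should be affected. Unmeasured differences in care-seeking remain, and the counts in item 3 are what would let a reader judge them.
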